##### Preference

Participants will answer the question: Between alternative (Table A) and current format (Table C) of SoF table, 'which table do you prefer?' It will be measured using a 7-point Likert-type scale (1 = I strongly prefer Table A, 2 = I prefer Table A, 3 = I somewhat prefer Table A, 4 = Same preference for Table A or C, 5 = I somewhat prefer Table C, 6 = I prefer Table C, 7 = I strongly prefer Table C), and it will be treated as a continuous outcome.

The outcomes considered in this trials are similar to the ones measured in previous randomized controlled trials and other observational studies testing SoF tables [16-18]. Table 2 presents a summary of outcomes measures.

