#### Blinding

The data collection process will be conducted automatically by the 'Survey Monkey' web platform. The SoF table formats will be labeled as A, or C; thus, participants will be allocated to Table A or C without any other information about the nature of the tables. Participants will be blinded to whether the table they are exposed to was the one in the current or alternative format while the outcomes understanding, accessibility, and satisfaction, are assessed. The only exception will be the outcome preference, as the only way to measure it is comparing the table to which they are randomized with the table to which they were not allocated. Therefore, participant blinding will be broken only after they have fully assessed the SoF table to which they were initially randomized. Once the data collection process is completed, the database will be prepared for statistical analysis and interpretation in a blinded fashion. Finally, the labels will be revealed after the analysis is done.

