### Inferential analysis

The primary outcome (understanding) will be estimated as the proportion of participants correctly answering each question per group. Data regarding this outcome will be analyzed using a multiple logistic regression per question, where the main predictor will be the arm to which participants were allocated (dichotomous - 2 categories). Other potential predictors to include in the model are participant strata (nominal - 3 categories), years of experience (nominal - 5 categories), familiarity with the GRADE approach (dichotomous - 2 categories), and previous education in health research methodology or epidemiology (ordinal - 3 categories). To adjust for multiplicity, the *P*-value will be modified using the Bonferroni correction for 7 multiple comparisons (<0.0035, CIs will be constructed with corresponding 1-sided z score 2.7).

For the secondary outcome, accessibility of information, we will calculate means, SDs and 95% CIs per domain. Data regarding this outcome will be analyzed using multiple linear regression where the main pre.dictor will be the arm to which participants were allocated (dichotomous - 2 categories). Other potential predictors included in the model will be participant strata (nominal - 3 categories), years of experience (nominal - 5 categories), familiarity with the GRADE approach (dichotomous - 2 categories), and previous education in health research methodology or epidemiology (ordinal - 3 categories). To adjust for multiplicity, the *P*-value will be modified using the Bonferroni correction for 4 multiple comparisons (<0.0125).

The secondary outcome, satisfaction, will be measured at an item level. The proportion of participants satisfied with either item included in Table A or C will be calculated per group.

For the secondary outcome, preference, linear regressions will be used. Since this outcome is obtained from a direct comparison of the tables (blinding is disclosed), there will be no main predictor of interest. However, we will control for the order in which the tables were shown to the participants (dichotomous - 2 categories). Other potential predictors to include in the model will be participant strata (nominal - 3 categories), years of experience (nominal - 5 categories), familiarity with the GRADE approach (dichotomous - 2 categories), and previous education in health research methodology or epidemiology (ordinal - 3 categories).

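### The plan lifts the blind to format status for the preference question, although comparing two tables only requires seeing both; label-driven bias could enter this secondary outcome.

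*Protocol article*

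**What the plan says.** Four places in the protocol article bear on this.

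- **Blinding** defines what is hidden: "Participants will be blinded to whether the table they are exposed to was the one in the current or alternative format". The means are neutral labels: "participants will be allocated to Table A or C without any other information about the nature of the tables". Preference is then excepted because "the only way to measure it is comparing the table to which they are randomized with the table to which they were not allocated", and the blind is broken once the allocated table has been fully assessed.
- **Preference** introduces the item with "Participants will answer the question: Between alternative (Table A) and current format (Table C) of SoF table, 'which table do you prefer". The seven response options name the tables only by letter, for example "1 = I strongly prefer Table A, 2 = I prefer Table A".
- **Inferential analysis** repeats the disclosure: "Since this outcome is obtained from a direct comparison of the tables (blinding is disclosed". For that reason there is no main predictor of interest. The regression controls for the order of presentation and may include participant characteristics. Evaluation of the models makes order the key predictor.
- **Satisfaction** gives a sample item that tells the participant a column was added to Table A and asks whether it should be available in later versions of these tables.

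**The concern.** The blind concerns the status of a table: established or new. Preference needs something else, namely sight of both tables. The Blinding section treats the second as if it required giving up the first.

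A participant who is told which table is the accepted format and which is the proposed replacement may lean towards the familiar or towards the new for reasons unrelated to layout. Every participant in both arms would receive the same information, so any such lean would be common to both arms. It would then be read as a preference for the layout. The last paragraph of the Background lists preference among the four criteria by which the new format is to be assessed, so the result will carry some weight even though it is secondary.

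**Working it through.** **Step 1. Does the stated reason support the disclosure?**

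| What is needed to ask preference | What the plan already has |
|---|---|
| Both tables visible | Yes: the other table is shown at the end (Overview of the design) |
| A name for each table | Yes: the labels A and C (Blinding) |
| A scale that refers to those names | Yes: all seven options use only Table A or Table C (Preference) |
| Knowledge of which table is current | Not needed for any of the above |

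The reason given supports the first row only. Nothing in the plan makes the last row necessary.

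**Step 2. Can the planned analysis remove a common shift?**

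Write the expected score as a + b × order + covariate terms, with order coded 0 or 1. Order is the same as allocation, because the allocated table is seen first. Suppose disclosure moves the mean score by d in both arms. The model becomes (a + d) + b × order + covariate terms. The order coefficient b does not change; the whole of d goes into the overall level. With no main predictor of interest, the overall level is what would be read as the preference result. Neither randomisation nor adjustment for order removes d.

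**Step 3. What could a shift do? (illustration only)**

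The protocol gives no figure for preference, so there is none to reproduce.

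Inputs:
- Completers: 308 × (1 − 0.10) = 277.2, taken as 277 (Sample size calculation).
- SD on the 1–7 scale: assumed, 1.5 to 2.0.
- Mean shift d when there is no true layout preference: assumed, 0.20 to 0.30.
- Test: overall mean against the neutral value 4, two-sided 5%. This is also assumed; the protocol does not specify it.

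Formulas: SE = SD/√277. Rejection probability = Φ(d/SE − 1.96) + Φ(−d/SE − 1.96).

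SE = 1.5/√277 = 0.090, and 2.0/√277 = 0.120.

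| Mean shift d | SD 1.5 | SD 2.0 |
|---|---|---|
| 0.20 | 60% | 38% |
| 0.25 | 79% | 55% |
| 0.30 | 91% | 70% |

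For d = 0.25 and SD 1.5: 0.25/0.0901 = 2.77, and Φ(2.77 − 1.96) = 79%; the second term is negligible. Using 280 participants instead of 277 changes these figures by less than one percentage point.

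**Step 4. Dilution by participants who recognise the current format.**

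The d in Step 3 is an average over all participants. If only a fraction f is newly informed and each of them shifts by s, then d = f × s. With f = 0.5 (assumed) and s = 0.25, d = 0.125, and the rejection probability falls to 28% (SD 1.5; 0.125/0.0901 = 1.39) or 18% (SD 2.0; 0.125/0.1202 = 1.04). The documents give neither f nor s.

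**The case against.** **The on-screen wording is not shown.** Under Preference, only the closing words of the item stand inside the inner quotation marks, and the response options are neutral. The lead-in may be addressed to the article's reader. This stands: a reader might infer that participants are certainly told which table is current, and the text does not establish that. But Blinding and Inferential analysis both say the blind is lifted. Either the form discloses status and should be changed, or it does not and those sections describe it wrongly.

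**Many participants would recognise Table C anyway.** Eligibility requires regular use of systematic reviews, recruitment runs partly through Cochrane groups, and the Background counts more than 600 published tables by 2014. This stands in part. Neutral labels help only those who would not recognise the format, and their number is unknown. Familiarity with GRADE is recorded as a two-category variable, so the plan allows for some who are unfamiliar.

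**The percentages prove nothing about bias.** This stands. They show only that an assumed shift of that size would often be statistically detectable, under an assumed SD and a test that the plan does not name. A reader might infer from them that the preference result will be biased, or in which direction. Nothing in the documents supports that, and novelty and status-quo effects act in opposite directions and may partly offset each other.

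**Rewording the preference item alone would not keep the blind.** This also stands. The sample satisfaction item already hints that Table A is the new one, and Overview of the design places satisfaction before the second table is shown.

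**Only one secondary outcome is touched, and the disclosure is stated openly.** Agreed, and this limits the weight of the point. Openness lets readers discount the result but does not let them separate label from layout.

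**Conclusion.** The point holds in a limited form. The plan says that participants' blinding to format status is lifted for preference, and the reason it gives does not require this. Novelty or status-quo bias could enter among participants who would not otherwise recognise the current format, and the planned adjustment for order would not remove a shift common to both arms.

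Direction and size are unknown. The range of 38% to 91% in the working is illustration, resting on an assumed uniform mean shift of 0.20 to 0.30, an assumed SD and an assumed comparison with 4. It falls if only some participants are newly informed.

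A reader might infer that the trial's main conclusion is compromised. It is not: non-inferiority is claimed on understanding, which is collected before the blind is lifted.

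**What to change.** 1. In the online form, show both tables as A and C and ask which the participant prefers, with no word that marks either as current, alternative or new. Reveal format status, if at all, only after preference is recorded.
2. Reword Blinding, Preference and Inferential analysis so that the exception for preference is that participants see both tables, not that the blind to format status is broken. If the form is already neutral, this text correction and item 3 are all that is needed.
3. Put satisfaction items that describe a feature as added, or refer to later versions, in neutral wording, or place them after the preference question.
4. Trials status says that recruitment is under way. Flag responses collected before any wording change so that they can be told apart in the preference analysis.

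The cost is a few edits to the form and three sections of text. No further participants are needed. Neutral wording would reduce the possible bias but not remove it, since some participants will still recognise the current layout.

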### Overview of the design

We will conduct a parallel-armed, non-inferiority randomized trial comparing a new alternative format of SoF tables with current format. We will contact systematic review users by Email and ask them to fill a questionnaire developed using the 'Survey Monkey' online system. The data collection form will include questions about baseline information (demographic characteristics, background, familiarity with systematic reviews and the GRADE system, and so on). Then, participants will be randomly assigned to one of two SoF tables, either the one in the alternative format or the one with the current format (See Figure 1). Randomization will be stratified according to participants’ background (health professional, guideline developer, researcher). They will be asked to answer questions to determine understanding, accessibility of information, and satisfaction with the table format to which they were allocated. Finally, we will show them the other table format to which they were not initially allocated in order to test their preference for either one.

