#### Randomization

Once the potentially eligible participants have completed the general information and background questionnaire, those who meet the selection criteria will be stratified according to self-reporting data as clinicians, guideline developers, or researchers and randomly allocated to one of the 2 SoF tables in a 1:1 ratio. To minimize missing data, the 'Survey Monkey' system will randomly assign participants to one of the SoF tables immediately after stratification, providing them with a link to access the questionnaires and tables.

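### The preference scale is printed in one direction for everyone, so a response-order or scale-end tendency cannot be told apart from true preference

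*Protocol article*

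**What the plan says.** The Preference section prints a single scale. Its low end is "1 = I strongly prefer Table A, 2 = I prefer Table A, 3 = I somewhat prefer Table A", its midpoint 4 means equal preference, and its high end is "5 = I somewhat prefer Table C, 6 = I prefer Table C, 7 = I strongly prefer Table C". The score is ordinal in form, but "it will be treated as a continuous outcome". The section introduces the item with "Between alternative (Table A) and current format (Table C) of SoF table" and then puts the question itself in quotation marks.

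Participants are "randomly allocated to one of the 2 SoF tables in a 1:1 ratio" (Randomization). After the other outcomes, "we will show them the other table format to which they were not initially allocated in order to test their preference for either one" (Overview of the design). Randomisation thus sets which table is seen first. Nothing in the article says that it also sets the direction of the preference scale.

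The Inferential analysis section states that preference comes from comparing the two tables directly and has no main predictor of interest, but "we will control for the order in which the tables were shown to the participants". Evaluation of the models makes that viewing order the key predictor for this outcome.

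**The concern.** Preference differs from the other scaled outcomes. The accessibility items also use fixed scales, but their means are compared between arms, so a habit of answering towards one end, if common to both arms, largely cancels. Preference has no such comparison: its meaning lies in where the overall score falls relative to the neutral point 4. If the printed layout pulls answers towards one end, that pull is part of the result in both arms.

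The plan already recognises one order effect in this outcome and adjusts for it. Viewing order and response-option order are separate factors, and the second is left constant. At stake is whether a modest departure of the mean from 4 can be read as users' preference or could be a product of the form.

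**Working it through.** The protocol gives no figure for this outcome to reproduce. The check has a structural part and an illustrative part.

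**1. Structure**

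For participant i, with all answers expressed in the printed direction, write

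Y = 4 + d − b·s + c·x + e

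- d: true preference (negative means Table A)
- b: scale-direction tendency; positive means towards the low end, negative towards the high end
- s: +1 if the scale is shown as printed, −1 if reversed
- x: viewing order, coded −0.5 or +0.5, set by the 1:1 randomisation
- c: viewing-order effect

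With the printed scale, s = 1 for everyone:

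- overall mean = 4 + d − b, so d and b cannot be separated;
- viewing-order contrast = c, so b cancels, but this contrast is not the preference result.

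If s is randomised independently of x, with half at +1 and half at −1, the average of s is 0. The overall mean is then 4 + d, and b is estimated from the coefficient of s.

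**2. Simulation of the same model**

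Assumed: 280 raters, SD 2.0, d = 0, b = 0.25, c = 0.40; 4,000 runs; viewing order in the model.

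| Scale | Overall mean | Viewing-order effect |
|---|---|---|
| Fixed direction | 3.75 | 0.40 |
| Direction randomised, answers recoded | 4.00 | 0.40 |

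Adjusting for viewing order leaves the whole 0.25 in place. Counterbalancing removes it and leaves the order effect intact.

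**3. Illustrative size**

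Inputs: 280 participants (Sample size calculation). Assumed, because the protocol does not give them: SD 1.5 to 2.0; shift 0.1 to 0.3 points towards Table A; a two-sided 5% test of the mean against 4.

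- SE = SD/√280 = 1.5/16.73 = 0.090, or 2.0/16.73 = 0.120
- P(false preference for A) = Φ(b/SE − 1.96), which is 2.5% at b = 0

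| Assumed shift b | SD 2.0 | SD 1.5 |
|---|---|---|
| 0.1 | 13% | 20% |
| 0.2 | 39% | 61% |
| 0.3 | 71% | 92% |

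For b = 0.2: 0.2/0.1195 − 1.96 = −0.29 gives 39%; 0.2/0.0896 − 1.96 = 0.27 gives 61%. By symmetry, the same shift towards Table C gives the same rates of false preference for C.

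**4. Why direction should not follow the allocated table**

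If the allocated table always took the low end, s would be fixed by viewing order (s = 2x or −2x). The order coefficient would become c − 2b or c + 2b, and a direction covariate could not be fitted beside it.

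**The case against.** A bipolar scale must put one table at one end, this one is symmetric and fully labelled, and the article contradicts nothing by printing it. Nothing in the article shows that a scale-end tendency exists here, or which way it would go. A pull towards the last option would favour Table C, and a pull towards the middle would favour neither. The article prints codes, not screens, and a condensed article may omit how the survey displays its options. The rates above depend on an assumed SD, an assumed shift and a test that the protocol does not specify. A mean of 3.8 would in any case lie nearest to the label for equal preference.

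All of this stands as a limit on size and certainty. It does not answer the structural point: as printed there is one direction, and neither randomisation nor the viewing-order covariate can separate its effect from preference.

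Three stronger readings are tempting and are not supported:

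- That participants read a question naming Table A first. The words "Between alternative (Table A) and current format (Table C) of SoF table" stand outside the quoted question and may be the authors' own description.
- That the layout favours the new format. The sign is unknown.
- That the case for adopting the new format is compromised. The non-inferiority claim rests on understanding, and the stated aim is to offer review authors additional options. Preference is one secondary outcome.

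**Conclusion.** The point holds as a low-cost design improvement. With the scale as printed, any response-order or scale-end tendency common to both arms enters the overall preference score in full. This rests on two readings: that the screen follows the printed coding, and that preference is judged from the overall score, as the absence of a main predictor of interest implies.

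The size is unknown. The 39% to 61% for a 0.2-point shift shows only that, with about 280 answers, the mean is estimated closely enough for a small artefact to look like a finding. It is not an estimate of what will happen in this trial. Understanding and accessibility are compared between arms and do not share the problem.

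**What to change.** For participants still to be recruited:

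- Randomise the scale direction independently of arm. If the item shown names both tables, randomise the naming order with it.
- Record the direction shown, and recode reversed answers to the printed direction (8 minus the answer).
- Include direction as a covariate, coded so that the reported overall score averages over the two directions. Keep it in the model regardless of the 10% change-in-estimate rule in Evaluation of the models: direction randomised independently of viewing order would hardly move the viewing-order estimate, so that rule would tend to drop it.
- Do not tie direction to the allocated table, because it would then be collinear with viewing order.

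The cost is a second variant of one question, one more random split, one recoding step and a small risk of coding error. The Trials status section says that recruitment is under way, so answers already collected keep the printed direction, and direction will be partly mixed with time of recruitment. The preference analysis should therefore also be shown for the counterbalanced participants alone. If the survey already rotates the options, a sentence saying so, with direction recorded and used in the analysis, is enough.

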**Table 2 Tab2:** **Overview of outcome measures**

**Outcome measures**	**Scale**	**Measure**	**Analysis method**
Primary			
Understanding	Dichotomous	% of participants with correct answers	Multiple logistic regression
Secondary			
Accessibility of information (at a domain level)	Ordinal (treated as continuous)	1-7 Likert scale	Multiple linear regression
Overall accessibility of information	Ordinal (treated as continuous)	1-5 Likert-type scale	Multiple linear regression
Satisfaction	Dichotomous	% of participants satisfied with an item	Chi-square test
Preference	Continuous	1-7 Likert scale	Multiple linear regression

### Sample size calculation

Sample size estimation was conducted using the software Stata/SE 10.1 (StataCorp., College Station, TX, USA) for Macintosh (Apple Inc., Cupertino, CA, USA). Based on the primary outcome, the null hypothesis was that the proportion of participants who answer the understanding questions correctly is lower in the alternative format table group compared to the current format table group, while the alternative hypothesis was that the proportion of participants correctly answering the questions in the alternative format table group is at least the same or higher compared to the current format table group (See Equation 1):

Null hypothesis1$$ {\mathrm{H}}_0:\ \mathrm{C}\mathrm{F}\ \mathrm{S}\mathrm{o}\mathrm{F}\ \mathrm{t}\mathrm{ables}\ \hbox{--}\ \mathrm{A}\mathrm{N}\mathrm{F}\ \mathrm{S}\mathrm{o}\mathrm{F}\ \mathrm{t}\mathrm{ables}\ {}^3\ \mathrm{N}\mathrm{IM}\left(\mathrm{C}\mathrm{F}\ \mathrm{is}\ \mathrm{superior}\ \mathrm{t}\mathrm{o}\ \mathrm{A}\mathrm{N}\mathrm{F}\right) $$

Alternative hypothesis2$$ {\mathrm{H}}_{\mathrm{a}:}\mathrm{C}\mathrm{F}\ \mathrm{S}\mathrm{o}\mathrm{F}\ \mathrm{t}\mathrm{ables}\ \hbox{--}\ \mathrm{A}\mathrm{N}\mathrm{F}\ \mathrm{S}\mathrm{o}\mathrm{F}\ \mathrm{t}\mathrm{ables}\ \le\ \mathrm{N}\mathrm{IM}\left(\mathrm{A}\mathrm{N}\mathrm{F}\ \mathrm{is}\ \mathrm{not}\ \mathrm{inferior}\ \mathrm{t}\mathrm{o}\ \mathrm{C}\mathrm{F}\right) $$

NIM: non-inferiority margin; CF: current format; ANF: alternative or narrative format

The proportion of participants correctly answering questions about understanding in similar randomized controlled trials that tested the current SoF table format was between 80 to 87% [17,18], and we expect, at least, the same percentage in the group of participants randomized to the alternative format of SoF table. A non-inferiority margin of 10% was set, and an allocation of 1:1 participants will be used. If there is truly no difference between the current and the alternative table format, then 280 participants are required to be 80% sure that the upper limit of a 1-sided 95% confidence interval (CI) will exclude a difference in favor of the current SoF table format of more than 10%. Assuming that 10% of participants would not complete the questionnaire, we aim to recruit a total of 308 participants. Linear and logistic regressions will be used as a method of analysis. According to Hsieh *et al*. [22], when more than one covariate is included in the model, a variance inflation factor should be added to the typical univariate analysis to obtain the required sample size. Equation 3 represents the variance inflation factor cited, where *b*_1_ represents the maximum likelihood estimate of *β*_1,_ var_p_(*b*_1_) corresponds to the variance of *b*_1_ that it is approximated from a one parameter model to a multivariate case when multiplied by 1/(1 - ρ^2^_1.23….p_), where ρ_1.23….p_ is the multiple correlation coefficient associating *X*_1_ with *X*_2_,…*X*_p_.

From unvariate to multivariate regression model sample size estimation:3$$ \mathrm{v}\mathrm{a}{\mathrm{r}}_{\mathrm{p}}\left({b}_1\right) = \mathrm{v}\mathrm{a}{\mathrm{r}}_1\left({\mathrm{b}}_1\right)/\left(1\hbox{-} {\uprho^2}_{1.23\dots .\mathrm{p}}\right) $$

Since this is a clinical trial in which participants will be allocated to the study arms randomly, it can be assumed that no correlation exists between being assigned to a particular arm and any of the predictors considered for analysis. Then, the value of ρ in the current study is zero, and the estimated sample size is the one described above.

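### The 80% power claimed for 280 participants assumes an unadjusted one-sided 5% interval and 87% correct answers; at the planned z = 2.7, power per understanding question is about 27% to 42%

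*Protocol article*

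**What the plan says.** **Sample size calculation.** The proportion answering correctly with the current format in similar trials "was between 80 to 87" per cent. "A non-inferiority margin of 10% was set", with 1:1 allocation. Taking the two formats to be equally good, the section states that "280 participants are required to be 80% sure that the upper limit of a 1-sided 95% confidence interval (CI) will exclude a difference" larger than the margin. The section adjusts this number for non-completion ("Assuming that 10% of participants would not complete the questionnaire, we aim to recruit a total of 308 participants") and considers a variance inflation for covariates, which it sets to nil. It does not mention multiplicity, and it does not say which value in the 80% to 87% range was used.

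**Inferential analysis.** Understanding is analysed question by question, with a "Bonferroni correction for 7 multiple comparisons (<0.0035, CIs will be constructed with corresponding 1-sided z score 2.7".

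**Claiming of non-inferiority.** The claim is made for a given question when the upper confidence limit is below 10%. No confidence level is given there.

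**Abstract.** The same rule is stated with a one-sided 95% interval, without adjustment.

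**Discussion.** The limitations say in general terms that the multiplicity adjustment may affect precision and lead to inconclusive results. No figure is given.

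**The concern.** The trial is sized for one critical value and analysed with a larger one. A larger multiplier widens every interval, so the upper limit falls below 10 points less often and the stated 80% no longer describes the planned analysis.

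The stake is interpretation. The protocol ties each question to a particular feature of the tables. If several questions fail to show non-inferiority, a reader who trusts the 80% figure may take this as doubt about those features of Table A, when two identical formats would often give the same picture at this sample size.

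**Working it through.** **Inputs.** Margin 0.10, true difference 0, 1:1 allocation, 80% power (z = 0.8416), one-sided 5% (z = 1.645), and a correct-answer rate p of 0.80 to 0.87, all from Sample size calculation; z = 2.7 from Inferential analysis. The check uses the unadjusted difference in proportions with the normal approximation.

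**Step 1: reproduce 280.** n per arm = 2p(1−p)(z + 0.8416)² / 0.10².
- p = 0.87: 0.2262 × 2.4866² / 0.01 = 139.9, so 140 per arm and 280 in total. This matches.
- p = 0.85: 316 in total.
- p = 0.80: 0.32 × 2.4866² / 0.01 = 197.9, so 198 per arm and 396 in total.
- p = 0.87 at one-sided 2.5%: 356 in total.

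So 280 rests on one-sided 5% and the top of the stated range.

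**Step 2: power at each critical value.** Power = Φ(0.10 / SE − z), with SE = √(2p(1−p)/n). With n = 140 per arm:
- p = 0.87: SE = 0.0402, ratio 2.488
- p = 0.80: SE = 0.0478, ratio 2.092

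| Critical value | Analysed | p = 0.87 | p = 0.80 |
|---|---|---|---|
| 1.645 | 280 | Φ(0.843) = 80.0% | Φ(0.447) = 67.2% |
| 2.45 | 280 | Φ(0.038) = 51.5% | Φ(−0.358) = 36.0% |
| 2.7 | 280 | Φ(−0.212) = 41.6% | Φ(−0.608) = 27.1% |
| 2.7 | 308 | 46.4% | 30.6% |

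Exact enumeration of the two binomials with a Wald interval, 140 per arm and z = 2.7, gives 43.2% and 27.5%. The approximation is adequate.

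**Step 3: where 2.7 comes from.** The one-sided tail beyond 2.7 is 0.00347. Now 0.025/7 = 0.00357, which fits the stated 0.0035. The level used for the sample size would give 0.05/7 = 0.00714 and z = 2.45. The analysis therefore departs from the sample size in two ways: it divides by seven, and it starts from 2.5% instead of 5%. At p = 0.87 the division alone takes power from 80.0% to 51.5%, and the change of starting level takes it on to 41.6%.

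**Step 4: totals that would give 80% power per question.**
- z = 2.7: 568 analysed (p = 0.87) to 804 (p = 0.80)
- z = 2.45: 492 to 694

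**Step 5: expected yield.** With identical formats and z = 2.7, the expected number of questions showing non-inferiority is 7 × 0.416 = 2.9 at 87% correct and 7 × 0.271 = 1.9 at 80%.

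**Step 6: dropout (minor).** 280 × 1.10 = 308, and 308 × 0.90 = 277.2 full completers; 280 / 0.90 = 311.1, so 312 with equal arms. At z = 2.7 and p = 0.87, 277 analysed give 41.1% instead of 41.6%.

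**The case against.** **A reader might infer that 42% is a ceiling.** The protocol does not support that. The 80% to 87% range is what earlier trials found, not a bound on each question here. With all 308 analysed, power at 87% is 46.4%. The Background cites 93% understanding with a Summary-of-Findings table; at that rate, 140 per arm and z = 2.7 give about 72%. The authors expect the alternative format to do at least as well; if it were truly 2 points better (89% against 87%), power would be about 65%. The 27% to 42% holds for the protocol's own sizing assumptions, and so do the expected counts.

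**A reader might also infer that every claim in the trial is judged at z = 2.7.** Only the understanding claims are. The secondary outcomes are tested for superiority; accessibility, for example, has its own correction for four comparisons.

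**Perhaps the unadjusted interval governs.** The Abstract says so, and the section on claiming non-inferiority is silent. On that reading 80% power at 87% would stand, but the Bonferroni rule would then have no effect. The Inferential analysis section is the more specific text, and the Discussion confirms that adjustment is intended, so z = 2.7 is the likelier reading. The conflict itself still has to be resolved.

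**The Discussion warns of inconclusive results.** It does, and that softens any charge of concealment. It gives no size, and the 80% figure stays uncorrected.

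**The dropout slip is trivial.** Agreed. The available-case analysis keeps answers given before a participant leaves, so some non-completers may still count for understanding, and the analysed number may exceed 277.

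**Conclusion.** The concern holds in this form: the 80% power stated for 280 participants does not apply to the Bonferroni-adjusted primary analysis. For 280 analysed, no true difference and 80% to 87% correct, power per understanding question is about 27% to 42% at z = 2.7, and 36% to 51.5% if the adjustment starts from the one-sided 5% level used for the sample size. The shortfall is thus present under either adjusted value. Even unadjusted, 80% is reached only at the favourable end of the range. The protocol also gives conflicting signals about which interval decides non-inferiority. These results rest on the normal approximation for an unadjusted difference in proportions.

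**What to change.** 1. Reconcile the Abstract, Sample size calculation, Inferential analysis and Claiming of non-inferiority on one confidence level and critical value for the understanding questions. Say whether the overall one-sided level divided by seven is 5% (z = 2.45) or 2.5% (z = 2.7).
2. Restate power per question at that value over the whole 80% to 87% range: 27% to 42% at z = 2.7, or 36% to 51.5% at z = 2.45, for 280 analysed.
3. State that 280 assumes 87% correct and a one-sided 5% level.
4. Withdraw the 80% power claim for the adjusted primary analysis, and put the restated figures beside the multiplicity limitation in the Discussion.
5. Minor: correct the inflation to 312, or say that 308 leaves about 277 full completers.

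The cost is wording, a less favourable power statement and at most four more recruits. This corrects the record but does not raise power. Reaching 80% per question would need the totals in step 4 of the working, which is a separate decision for the investigators. Recruitment is already under way, so the restatement should be on record before results are seen.
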